## Method/design

### Trial treatments/study procedures

Patients on the treatment arm of the trial will receive ESWT using the PiezoWave2 shockwave system, in accordance with the manufacturer’s instructions and unchanged from its current clinical use at 100 impulses 0.1 mJ/mm per cm^2^. Trained staff will provide all treatments, including sham treatment. Both local research and development and medical physics departments deem this device low risk and safe to use. The device will be targeted at the gastrocnemius muscles of the affected lower leg for several minutes at each treatment session. Participants in the control group will undergo an identical process as if treatment were being given but with the shockwaves not being administered and the sham treatment described above alternatively used.

1 shockwave session = 100 impulses per cm^2^ covering two areas per affected leg, with one (6 cm × 5 cm) on the medial head of the gastrocnemius and one (6 cm × 5 cm) on the lateral head of the gastrocnemius. This calculates as 6000 impulses/5 Hz/0.1 mJ/mm^2^ in total.

### Environmental conditions

A designated clinical room in the vascular laboratory at Hull Royal Infirmary will be used for all examination and treatments. The device will be applied to the gastrocnemius muscle of the affected limb/s at two sites (medially and laterally). One course of treatment will consist of three separate treatment sessions per week on alternate days for 3 weeks.

### Outcome measurements

#### Primary outcome

The primary outcome is the short-to-medium term effect of ESWT in comparison to sham treatment on MWD in patients suffering intermittent calf claudication at baseline, 4 weeks, 8 weeks and 12 weeks post therapy.

#### Secondary outcomes

The secondary outcomes are as follows:Claudication distance (CD) — the distance covered prior to onset of any symptoms — at baseline, 4 weeks, 8 weeks and 12 weeks post therapyPre and post treatment ABPI at baseline, 4 weeks, 8 weeks and 12 weeks post therapyPatient reported walking distance (PRD) at baseline, 4 weeks, 8 weeks and 12 weeks post therapyAcceptability and tolerability of the treatment measured by VAS after each individual treatment sessionControl group patients will be asked to complete tolerability questionnaires as if they were receiving active treatment.
Quality of life as measured by SF-36 at baseline, 4 weeks, 8 weeks and 12 weeks post therapyQuality of life as measured by the EQ-5D at baseline, 4 weeks, 8 weeks and 12 weeks post therapy

### Assessments

Following completion of the consent procedure, baseline data will be collected as defined above. Outcome measurements will then be recorded according to the subsequent study visits. See Fig. 1 and Table 4.

**Fig. 1 Fig1:**
[figure not shown]
Consolidated Standards of Reporting Trials (CONSORT) flow diagram

#### Assessments prior to the first ESWT therapeutic session

Assessments prior to the first EWST session are:PRDABPIClaudication distanceMaximum walking distanceQuality of life questionnaires (SF-36 and EQ-5D)

#### Assessments during all therapeutic treatments

During all therapeutic treatments, we will assess:Pain rating of treatment using VASQuality of life questionnaires (SF-36 and EQ-5D)

#### Assessments during weeks 4, 8 and 12 follow-up appointments

Assessments at weeks 4, 8 and 12 are:Tolerability questionnaire (week 4 only)PRDABPIClaudication distanceMaximum walking distanceQuality of life questionnaires (SF-36 and EQ-5D)

### Concurrent medications

The study will not influence clinical management of the patient; therefore, there are no restrictions of prescribed medication. Researchers will monitor concomitant medications taken by the patients at screening and during the entire study period.

### Adverse events

Serious adverse events will be reported to the Sponsor and the National Research Ethics Service (NRES) recognised Research Ethics Committee (REC).

### The device

The device being used in this trial is the PiezoWave 2. Training and support are provided by Impact Medical, Liverpool, UK.

### Safety and tolerability

The device is a CE-marked (CE 93/42/EEC) British Standards Institute, notified body 0086), commercially available device. Trained staff will manage the device and are responsible for applications of treatment. The facilities where participants will be assessed are fully equipped for all emergency situations.

### Safety reporting

The safety definitions are given below.

*Adverse event* (*AE*): An AE is any untoward medical occurrence in a subject to whom a medicinal product has been administered as part of a research study, including occurrences which are not necessarily caused by or related to an investigational medicinal product (IMP).

*Adverse reaction* (*AR*): An AR is any untoward and unintended response in a subject to an IMP which is related to any dose administered to that subject.

Important medical events that may not be immediately life-threatening or result in death or hospitalisation but may jeopardise the patient or may require intervention to prevent one of the other outcomes listed in the definition above should also be considered serious.

*Serious adverse event* (*SAE*): An SAE is an event not related or unlikely to be related to the IMP. An adverse event becomes serious if it:Results in deathIs life-threateningRequires hospitalisation or prolongation of existing hospitalisationResults in persistent or significant disability or incapacityIs a congenital anomaly or birth defect

*Serious adverse reaction* (*SAR*): A SAR is a serious event which is suspected (possibly, probably or definitely) to be related to an IMP and expected for the IMP.

*Suspected unexpected serious adverse reaction* (*SUSAR*): A SUSAR is a serious event which is suspected (possibly, probably or definitely) to be related to an IMP and unexpected for the IMP, i.e. not previously documented in any of the IMP information (investigator brochure, Summary of Product Characteristics, patient information leaflet) or protocol on device deficiencies.

*Device deficiency*: A device deficiency is an inadequacy of a medical device with respect to its identity, quality, durability, reliability, safety or performance. All device deficiencies will be recorded and reported accordingly.

*Anticipated and unanticipated serious adverse device effects* (*SADE*/*USADE*): There are no known SADEs with this device; therefore, all SADEs are, by definition, unanticipated.

If a USADE is suspected, no additional patients will be enrolled until the cause of the event and its relationship to the study device have been determined. If the event is device-related, the following action will be necessary. If there is a specific type of patient who is vulnerable to the event, then the inclusion/exclusion criteria will be amended to exclude this ’at risk’ group.

The protocol procedures may be revised including but not limited to the duration of therapy. The study may also be stopped. See Table 2.

**Table 2 Tab2:** Summary of adverse events

Adverse events	Non-device-related	Device-related	
Non-serious	Adverse event (AE)	Adverse device effect (ADE)	
Serious		Serious adverse device effect (SADE)	
		Anticipated	Unanticipated
		Anticipated serious adverse device effect (ASADE)	Unanticipated serious adverse effect (USADE)

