### Causality and adverse device effects

The relationship of both AEs and SAEs to the study device will be determined as follows (Table 3).

**Table 3 Tab3:** Causality of adverse events

Causality	Definition
Almost certainly	Starts within a time related to the operation of the device, and No obvious alternative medical explanation
Probably	Starts within a time related to the operation of the device, and Cannot be reasonably explained by known characteristics of the patient’s clinical state
Possibly	Starts within a time related to the operation of the device, and A causal relationship between the operation of the device and the adverse event is at least a reasonable possibility
Unrelated	The AE is definitely not associated with the study device

The Investigator must endeavour to obtain sufficient information to determine the causality of the AE and must provide his/her opinion of the causal relationship between each AE and the study device. This may require instituting supplementary investigations of significant AEs based on their clinical judgement of the likely causative factors and/or include seeking a further opinion from a specialist in the field of the AE.

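### The SAE definition requires that the event be unrelated to the product; this contradicts the protocol's own causality and SAE-form rules and, read literally, leaves serious device-related events without a stated Sponsor/REC report

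*Protocol article*

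**What the plan says.** All references are to the protocol article.

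- **Safety reporting, SAE definition:** "An SAE is an event not related or unlikely to be related to the IMP". A list of seriousness criteria follows (death, threat to life, hospitalisation and so on), with no reference to cause.
- **Safety reporting, AE definition:** "An AE is any untoward medical occurrence in a subject to whom a medicinal product has been administered as part of a research study". The AR, SAR and SUSAR definitions likewise depend on an investigational medicinal product (IMP).
- **The device:** "The device being used in this trial is the PiezoWave 2".
- **Safety reporting and Table 2:** a serious device-related event has its own label, "Serious adverse device effect (SADE"), divided into anticipated and unanticipated. The text adds: "There are no known SADEs with this device; therefore, all SADEs are, by definition, unanticipated".
- **Adverse events:** "Serious adverse events will be reported to the Sponsor and the National Research Ethics Service (NRES) recognised Research Ethics Committee (REC").
- **Causality and adverse device effects:** "The relationship of both AEs and SAEs to the study device will be determined as follows", followed by the four grades of Table 3.
- **Adverse event and device deficiency reporting:** all AEs go on the AE page of the case report form, every event judged serious also gets an SAE form, and SAEs reach the Principal Investigator within 24 hours.

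**The concern.** Seriousness and causality are separate attributes of an event. Seriousness is normally judged first and decides what must be reported; relatedness is judged afterwards. Here relatedness is built into the definition of the reportable class, and in the wrong direction: an event thought to be caused by the treatment stops being an SAE. Since the Sponsor/REC rule is written for SAEs, the events of most interest in a device trial are the ones it does not plainly reach.

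At stake is whether site staff, following the text, would know that a serious event attributed to the shockwaves must go to the Sponsor and the REC. The Discussion gives safety and tolerability as the first purpose of the study, so this should not depend on guessing the intent.

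**Working it through.** No arithmetic applies. The check is to read every safety definition and reporting sentence side by side.

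**Step 1. What does the SAE definition cover?** There are two readings of IMP.

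- *IMP means the study device.* A serious event judged possibly, probably or almost certainly related (three of the four grades in Table 3) is then not an SAE as defined. It is a SADE and, since none are known for this device, an unanticipated one (USADE).
- *IMP is taken literally.* The trial treatment is a device, so the relatedness condition refers to nothing, and the AR, SAR and SUSAR definitions do not fit the trial.

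The definition is defective on either reading.

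**Step 2. Does the rest of the document agree with it?**

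- The criteria directly after it decide seriousness by outcome alone.
- The causality section grades SAEs for relationship to the device. That would be pointless if SAEs were unrelated by definition.
- The SAE form is triggered by seriousness alone.
- Table 3 has no grade for an unlikely relationship, although the definition relies on one. Such an event has no matching grade, and if it is graded as possible it leaves the defined SAE set.

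So the definition stands against three other statements in the same document.

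**Step 3. Which events have a stated route to the Sponsor and the REC?**

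| Item | What is stated | Sponsor/REC report of the event? |
|---|---|---|
| SAE | SAE form, Principal Investigator within 24 hours, follow-up to resolution, Sponsor and REC | Yes |
| SADE/USADE | On suspicion of a USADE, enrolment is held while the cause is examined; eligibility or procedures may be changed, or the study stopped | Not stated |
| SAR/SUSAR | Definition only | Not stated |
| Device deficiency | Recorded and reported, no recipient named; concerns faults of the device, not patient events | Not stated |
| Termination for safety (Study completion or discontinuation) | Regulators and REC informed | Concerns the study, not an individual event |

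**Step 4. Combine.** On the device reading, a serious device-related event goes on the AE page and an SAE form, is graded for causality, and may halt enrolment. The one rule that names the Sponsor and the REC as recipients does not reach it as the terms are defined. If SAE is read in the wider sense of Step 2, the same rule does reach it. The two readings give different reporting duties for the same event.

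**The case against.** The strongest reply is that this is one badly worded sentence and that the intent is clear. The next sentence defines seriousness properly, the causality and form rules treat SAEs as possibly device-related, and serious device effects bring the firmest response in the document. A journal article may also leave detailed reporting routes to the full protocol.

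Much of this stands. The intent was probably to report all serious events, and data capture does not depend on causality. But the definition is given in full and is wrong as given, so it is not a detail left out for brevity. A reader has to override it to reach the intended rule.

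Four stronger readings are tempting and are not supported:

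- *The safety comparison would favour active treatment because related events drop out of the SAE count.* The article plans no comparison by arm restricted to SAEs as defined, and related serious events would still be on the AE page and the SAE form.
- *The defect can be sized by an upper confidence limit for zero events in the treated arm.* The article gives a maximum of 100 participants and no allocation ratio. Such a limit would in any case measure precision, not the effect of the definition.
- *No participant can have an AE, since none receives a medicinal product in the trial.* This is too literal. Table 2 classifies AEs by relation to the device, and Table 4 gives bruising and bleeding as examples.
- *The SAR definition contradicts the statement that no serious device effects are known.* It does not. The SAR class is simply empty, and a related serious event counts as unexpected.

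**Conclusion.** The point holds as an internal contradiction with a consequence for safety reporting. The SAE definition makes unrelatedness, or unlikely relatedness, a condition. It conflicts with the seriousness criteria, the causality section and the SAE-form rule, and it uses medicinal-product terms in a device trial. On a literal reading, serious device-related events fall outside the only stated event-level report to the Sponsor and the REC.

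The size is qualitative. The gap concerns the stated recipients of a report, not the recording of events, and it matters only if such an event occurs. The primary outcome, maximum walking distance, is unaffected. The conclusion rests on reading IMP as the study device; on the literal reading the definition fails for a different reason. It does not rely on the serious, non-device-related cell of Table 2, which appears blank here and may have been lost when the text was extracted.

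**What to change.** Amend the wording in four places:

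1. **AE:** define it by reference to the study device or study procedures, active or sham, so that both arms are plainly covered.
2. **SAE:** delete the relatedness condition and define an SAE as any AE that meets a listed seriousness criterion, regardless of causality. Leave relatedness to Table 3.
3. **Terms:** replace AR, SAR and SUSAR with the device terms already in use: ADE, SADE, and ASADE or USADE.
4. **Adverse events section:** state that the report to the Sponsor and the REC covers all SAEs, including SADEs and USADEs.

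The actions that follow a suspected USADE need no change for this point. The cost is a definitions amendment and a matching check of the case report form labels; no extra data or visits are needed.

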### Causality and adverse device effects

The relationship of both AEs and SAEs to the study device will be determined as follows (Table 3).

**Table 3 Tab3:** Causality of adverse events

Causality	Definition
Almost certainly	Starts within a time related to the operation of the device, and No obvious alternative medical explanation
Probably	Starts within a time related to the operation of the device, and Cannot be reasonably explained by known characteristics of the patient’s clinical state
Possibly	Starts within a time related to the operation of the device, and A causal relationship between the operation of the device and the adverse event is at least a reasonable possibility
Unrelated	The AE is definitely not associated with the study device

The Investigator must endeavour to obtain sufficient information to determine the causality of the AE and must provide his/her opinion of the causal relationship between each AE and the study device. This may require instituting supplementary investigations of significant AEs based on their clinical judgement of the likely causative factors and/or include seeking a further opinion from a specialist in the field of the AE.

### Adverse event and device deficiency reporting

All AEs during the study will be reported on the Adverse Event page of the Case Report Form (CRF). If events are deemed serious, a separate Serious Adverse Event form will also be completed.

Device deficiencies during the study will be recorded on a dedicated form. The Principal Investigator will record the action taken to alleviate the AE/SAE. AEs may be recorded as ongoing at the end of the study, but SAEs will be followed up until resolved. Trained medical personnel will be accessed to act with appropriate diagnostic and therapeutic measures until the subject has recovered. SAEs will be reported to the Principal Investigator within 24 hours.

### Withdrawals and dropouts

During the study, treatment may be discontinued for many reasons such as the occurrence of a disease, an AE that could interfere with the subject’s evaluation or simply upon the subject’s request to discontinue for any reason. Concurrent medical events that do not interfere with scheduled testing and that are judged by the Investigator to not have an effect on the outcome measures will not disqualify a subject from continuing in the study. If a subject is withdrawn from the study because of an AE, treatment discontinuation must be explained on the Adverse Event page of the CRF.

Patients will be advised that they are free to withdraw from the study at any time for any reason or, if necessary, the Investigator may withdraw a subject from the study to protect the subject’s health. The Investigator may withdraw a subject from the study if it is considered that the scientific, and therefore, ethical standards of the study are compromised. Patients may also be withdrawn for not complying with study procedures. The type and timing of the withdrawal for withdrawal will be fully recorded on the CRF. Should a patient choose to withdraw from treatment, they will be asked if they are still available for follow-up data collection.

### Trial exit

Participants will exit the trial completely if:They have completed their participationThey request to/are unable to continue being followed upThey experience an AE (if the AE is deemed due to trial involvement) such that they are unable to complete follow-upThey die

### Overall timescale for the study

Recruitment began as soon as all necessary approvals (REC, Medicines and Healthcare products Regulatory Agency (MHRA) and Trust R&D) were obtained. The intention is that recruitment will run until a power calculation of participant number is reached. A power calculation will be performed from ongoing cohort study and existing evidence with a maximum of 100 participants in total. Patients are involved in the trial for 12 weeks only.

The outline of events is given in Table 4.

**Table 4 Tab4:** Standard Protocol Items: Recommendations for Interventional Trials (SPIRIT) diagram of events timeline

	Study period						
	Enrolment and screening	Allocation	Post randomisation				Exit
Timepoint			Treatment period	4/52 F/U	8/52 F/U	12/52 F/U	
Enrolment:							
Eligibility screen	X						
Demographics	X						
Past medical history	X						
Provision of Patient Information Sheet	X						
Informed consent		X					
Randomisation/allocation		X					
Interventions:							
Active shockwave treatment (Group A)			9 sessions (3 × per week for 3 weeks)				
Sham treatment (Group B)			9 sessions (3 × per week for 3 weeks)				
Assessments:							
Ankle-brachial pressure index	X			X	X	X	
Claudication distance	X			X	X	X	
Maximum walking distance	X			X	X	X	
SF-36 questionnaire	X			X	X	X	
EQ-5D questionnaire	X			X	X	X	
Patient tolerability VAS			Recorded after each treatment				
Adverse events (bruising, bleeding, etc*.*)			Recorded after each treatment	X	X	X	

### Study completion

Completion refers to the date of final data collection from the last patient. Paper records from the trial will be stored for 5 years from trial end.

Data will be collected and collated using a specifically designed database which will be kept on hospital central servers on a limited access hard drive. Access will be via password-protected log-in on hospital servers only and will be limited to members of the Academic Vascular Surgery Unit. The file itself will have password-protected opening. Electronic records will be stored for 5 years from trial end.

### Data management

The use and control of all data will comply at all times with the requirements of the Data Protection Act 1998. The Principal Investigator of the study will register with the local Data Protection Officer. All data management procedures will be detailed and referred to as the Data Management Plan. All data will be entered and checked by a second person.

The database will be designed and built by the research team using Microsoft Excel. Appropriate CRFs will be prepared for the collection of the data requested by the protocol. All response variables will be entered into the database by the data management personnel.

### Statistical considerations

Statistical advice has been sought from the Statistical Consultancy Service (Hull York Medical School, University of York) in preparing this protocol. Further review will be sought when all results have been collected and the analysis performed.

Data will be analysed as intention to treat. The SPSS computer package will be used with a *p* value of <0.05 taken as the level of significance.

#### Sample size calculation

A power calculation will be performed from the ongoing cohort study and existing evidence with a maximum of 100 participants in total.

#### Analysis

Data will be analysed on an intention-to-treat basis. The main aim is to provide estimates of distribution and variability of outcomes with comparisons made between the shockwave treatment group and sham group. These will be expressed principally as means or medians and confidence intervals.

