#### Primary outcome

The primary outcome is the effect of extracorporeal shockwave therapy in comparison to sham treatment on the maximum walking distance (MWD) — the distance covered before the subject is unable to continue — at baseline and at 4 weeks, 8 weeks and 12 weeks post therapy.

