### Screening and evaluation

Patients identified as potential participants will undergo a screening interview.

Baseline data will be collected from all consenting participants. Data collected will include:Evaluation of compliance with inclusion and exclusion criteriaIssue of Patient Information Sheet if not already issued
Informed consent (24 hours later)Participant’s name and address and, if used by the participant, mobile telephone number and email address (for the receipt of follow-up questionnaires) and date of birthDetails on participant’s general practitionerDemography and medical historyPhysical examination to include palpation of lower limb pulsesAnkle-brachial pressure index (ABPI)Vital signsAssessment of any concurrent medicationsPregnancy test if necessaryBody mass index (BMI)Smoking historyBaseline quality of life

Appropriately screened and consented individuals will be further assessed as follows:Baseline visitPatient reported walking distance (PRD)Vital signsQuality of lifeTreadmill assessment to report intermittent claudication distance (ICD) and maximum walking distance (MWD)For treadmill walking distances, ICD and MWD will be measured on a treadmill at 2.5 km/h at a 10° incline for up to 10 minutes. Participants will be asked to rest for 30 minutes prior to testing to ensure a resting state and negate effects of mobilising to the vascular laboratory.Randomisation will occur at the end of the baseline visit via sealed envelope software to either active treatment or control group by a second investigator. The treatment will then proceed as follows:(e)The second investigator will then perform ESWT therapy for the active group and sham treatment for the control group. Sham treatment will be delivered by setting the generator to off and replicating the sound of the active treatment via an audio recording emitted from the machine(f)All patients will then complete a tolerability questionnaire for the ESWT treatment.

Weeks 1, 2, 3 visitsVital signsESWT performed by second investigator with pulsewave generator on for active group and off for control groupPatient to complete tolerability questionnaire for ESWT treatmentPRD recordedAssessment of any concurrent medicationsAssessment of any adverse events
Week 4, 8, 12 visitsPRDVital signsQuality of lifeTreadmill assessment to report ICD and MWDAssessment of any concurrent medicationsAssessment of any adverse events

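### The group comparison is left open between means and medians, and baseline MWD, measured in everyone before randomisation, has no stated role in it; one prespecified baseline-adjusted analysis should be named

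*Protocol article*

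**What the plan says.** The analysis text in the protocol article is short.

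- **Analysis** sets the aim as "estimates of distribution and variability of outcomes with comparisons made between the shockwave treatment group and sham group", and continues: "These will be expressed principally as means or medians and confidence intervals". The population is fixed: "Data will be analysed on an intention-to-treat basis".
- **Statistical considerations** adds SPSS and a p "value of <0.05 taken as the level of significance". It says statistical advice was taken in preparing the protocol, and places further statistical review after results have been collected and analysed.
- **Primary outcome** defines the effect on MWD "at baseline and at 4 weeks, 8 weeks and 12 weeks post therapy", so baseline is listed among the outcome times.
- **Screening and evaluation** puts the treadmill test at the baseline visit, and "Randomisation will occur at the end of the baseline visit". Baseline MWD is thus a pre-randomisation measurement.
- The same section fixes the test: "ICD and MWD will be measured on a treadmill at 2.5 km/h at a 10° incline for up to 10 minutes".
- **Sample size calculation** defers the calculation, "with a maximum of 100 participants in total".

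Neither analysis section names a test, model, covariate, scale or primary visit. Neither calls the comparison adjusted or unadjusted.

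**The concern.** Two things are at stake.

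**The effect measure is open.** A difference in means and a difference in medians are different quantities. MWD has a hard upper limit from the 10-minute test and may be skewed, so the two can diverge. The protocol names both and gives no rule, and the only further statistical input it describes comes after the results are in. A reader of the final report could not tell from this document which measure was meant to be primary.

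**Baseline MWD has no stated role.** Summarising each arm by its mean or median at a follow-up visit makes no use of each patient's own starting distance. With recruitment capped at 100, precision cannot be bought by enlarging the trial, so information already collected is the obvious place to find it.

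**Working it through.** The protocol states no power, effect size, SD or calculated sample size, so there is no figure to reproduce. The check is what baseline adjustment would be worth.

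**Inputs from the protocol article**
- Maximum N = 100 (Sample size calculation).
- Significance level 0.05 (Statistical considerations); two-sided is assumed, as sidedness is not stated.
- Treadmill at 2.5 km/h for at most 10 minutes (Screening and evaluation).

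**Assumed inputs**
- 1:1 allocation at the cap, so 50 per arm. The ratio is not stated, and the cap is not a target.
- Baseline to follow-up correlation r = 0.5 to 0.8, with 0.3 as a low case.
- A true difference of 0.4 SD, for illustrating power only.

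**Step 1: gain against a follow-up-only comparison.** ANCOVA multiplies the variance by 1 − r², so the equivalent sample multiplier is 1/(1 − r²).

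**Step 2: gain against change from baseline.** With equal SDs at both times, change has variance factor 2(1 − r). Since 1 − r² = (1 − r)(1 + r), the multiplier is 2(1 − r)/(1 − r²) = 2/(1 + r).

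| r | 1 − r² | Multiplier vs follow-up only | Multiplier vs change |
|---|---|---|---|
| 0.3 | 0.91 | 1.10 | 1.54 |
| 0.5 | 0.75 | 1.33 | 1.33 |
| 0.7 | 0.51 | 1.96 | 1.18 |
| 0.8 | 0.36 | 2.78 | 1.11 |

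**Step 3: cost of estimating one covariate.** At N = 100 the efficiency factor is about 96/97 = 0.990, a loss of about 1%. The multipliers 1.33 and 2.78 become 1.32 and 2.75.

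**Step 4: power and detectable difference, 50 per arm.** Power is from the noncentral t with noncentrality 0.4/√(1 − r²) × √(50/2). The detectable difference at 80% power is 0.566 SD × √(1 − r²).

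| Analysis | Noncentrality | Power at 0.4 SD | Detectable difference at 80% power |
|---|---|---|---|
| Follow-up only | 2.00 | 51% | 0.57 SD |
| Adjusted, r = 0.5 | 2.31 | 63% | 0.49 SD |
| Adjusted, r = 0.7 | 2.80 | 79% | 0.40 SD |
| Adjusted, r = 0.8 | 3.33 | 91% | 0.34 SD |

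**Step 5: the treadmill ceiling.** 2500 m / 60 min × 10 min = 416.7 m. A simulation with log-normal MWD (assumed medians 100 to 200 m, log-SD 0.6 to 0.8), capped at that distance, put between 1% and 18% of baseline values at the cap. The follow-up-only multipliers became:
- log scale: 1.29 to 1.33 at r = 0.5, and 2.56 to 2.76 at r = 0.8;
- raw scale: 1.27 to 1.29 at r = 0.5, and 2.36 to 2.50 at r = 0.8.

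Under these assumptions the cap trims the gain and does not remove it, on either scale.

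**The case against.** The strongest reply is that the Analysis section describes how results will be expressed, not how they will be modelled. Baseline-adjusted means with confidence intervals would fit the sentence equally well. Model, covariates and transformation are commonly left to an analysis plan, none is shown here, and a journal article condenses further. This stands. A reader might infer that the plan commits to an unadjusted comparison, or that the choice between mean and median will be made on the data. The document shows neither: it is silent on the first, and on the second it only fails to exclude it.

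The reply also holds on these points:

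- **Comparator.** Baseline is listed within the primary outcome, which suits a change or longitudinal analysis at least as well as a follow-up-only one. The multiplier of 2.78 applies only against follow-up only; at the same correlation it is 1.11 against change.
- **Assumed correlation.** The range 0.5 to 0.8 has no source in the document, and at 0.3 the follow-up-only gain is 1.10.
- **Log scale.** The article gives no MWD distribution, so a log scale and a ratio of geometric means are options and not requirements. Logs do not deal with values at the treadmill limit.
- **Chance imbalance.** With 50 per arm, the baseline difference has a standard error of √(2/50) = 0.2 SD. A reader might call an imbalance of that order a bias. Under randomisation it is part of the sampling variability that a valid confidence interval already covers, so it restates the precision argument and is not a second defect.

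None of this supplies a rule for choosing between means and medians. That gap is in the stated text, and closing it depends on no assumed correlation.

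**Conclusion.** The point holds in a limited form. The protocol states how the primary comparison will be expressed, leaves two effect measures open without a selection rule, and gives a pre-randomisation measurement of the same outcome no stated role in a trial that cannot exceed 100 participants. One prespecified baseline-adjusted analysis would settle the measure and improve precision whether the alternative is follow-up only or change from baseline. How much it improves is uncertain: it could be large if follow-up values alone would otherwise be compared and the correlation is high, and modest if change would be analysed or the correlation is low. The sizes rest on 50 per arm, two-sided testing and an assumed correlation, so they illustrate what is at stake and do not measure a known loss. This is a recommended improvement to the plan, not an error that invalidates the trial.

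**What to change.** Before unblinding, and while the trial is still recruiting as its Trial status section reports, state in the protocol or analysis plan:

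1. One primary effect measure for MWD.
2. One baseline-adjusted primary analysis: ANCOVA, or a repeated-measures model over weeks 4, 8 and 12, with baseline MWD as covariate, reported with a 95% confidence interval.
3. The scale of analysis, and how values at the 10-minute limit (about 417 m) are handled.
4. Raw means and medians as descriptive summaries only.
5. Baseline adjustment likewise for secondary outcomes that have a baseline value (claudication distance, ABPI, patient reported walking distance, SF-36, EQ-5D), each on a scale that suits it.

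The cost is analysis wording plus the roughly 1% efficiency loss for one covariate. No new data or visits are needed, and SPSS fits these models. If a log scale is chosen, the effect becomes a ratio of geometric means, and the text should say so.
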